**Figure 3 figure3:**
[figure not shown]
Schematic representation of the medical procedure and the patient-caregiver interaction in the asymmetric game design.

#### Control Condition: Audio Recordings of Ocean Waves

The research field of environmental psychology explores the positive effects of natural environments on human experience [24], including in medical contexts [25,26]. It has been shown that exposure to natural environments can reduce acute and anticipatory stress. Annerstedt et al [27] showed a stress-recovery–promoting effect of birdsong in a virtual forest scenario. Liszio et al [28] have shown that the audiovisual presentation of virtual underwater environments significantly reduces acute and anticipatory stress. However, research on the effect of solely auditive presentation of nature sounds on the emotional experience of patients in medical situations is scarce; however, there is some evidence in the literature. Moreover, several studies indicate a significant reduction of patient anxiety and agitation during percutaneous coronary intervention [29] and coronary artery bypass graft surgery [30,31] when listening to nature sounds.

In the control condition, a 30-minute recording of ocean waves will be played instead of the VR game. Recording will start with a 1-minute introduction by the same soothing voice that narrates the companion character “Turtle” in SDVR. From then on, only the sound of the waves will continue.

#### Hardware

Patients in the VR condition will play the game with a Pico G2 4K HMD (Figure 4, left). The device is a stand-alone HMD in which all calculations are performed on the device itself, so that no additional computer is required. The HMD has 3 df and can therefore only be used when sitting or lying down. User inputs are made via the associated controller, which resembles a simple remote control. A larger touchpad is located on the controller, which works like the directional pad on a typical game controller. In addition, the controller has a trigger button that is operated with the index finger. It can be controlled with 1 hand using either the left or right hand. We chose this hardware for the following reasons: the housing is comparatively easy to disinfect, as all external components are either hard plastic or rubber. Comparable devices from other manufacturers typically use foam covered with fabric for the face pad and elastic fabric for the headbands, which do not meet health care hygiene standards. Furthermore, no user account from third-party providers is required for operation. Apps can also be started in a so-called kiosk mode, that is, the corresponding app starts automatically when the device is switched on, which makes it much easier to use in the fast pace of everyday clinical practice. Finally, the standard controller’s small design and reduced number of buttons simplify operation with small hands. Children have no problems holding the controller and reaching all the buttons with their fingers. The symmetrical design allows operating the controller with either the left or right hand.

For the caregiver, we will use a conventional gamepad as an input device for the game. The gamepad and HMD are connected via Bluetooth. The advantage of using a common gamepad is that many people are familiar with the layout of the buttons and the handling while the acquisition costs are low.

For data collection, we will use tablet PCs. These will also be used to play the recording of ocean waves in the control condition.

**Figure 4 figure4:**
[figure not shown]
The Pico G2 4K head-mounted display with controller (left) and conventional gamepad (right) used in the experimental condition during the medical procedure.

### Psychometric Assessment

#### Emotional Experience

##### State and Trait Anxiety

The State-Trait Anxiety Inventory is an established questionnaire for measuring anxiety [32] (Table 1). It was developed to measure both state anxiety and the personality characteristics of anxiety (ie, trait anxiety). The questionnaire consists of 2 scales, one for assessing state anxiety and one for assessing trait anxiety. In this study, we will use the German translation provided by Laux et al [33].

For the child survey, we will use the German translation of the adapted State-Trait Anxiety Inventory for Children [19]. This adaptation is characterized by a reduced number of 20 per scale items and a simplified response scale as compared to the original State-Trait Anxiety Inventory. In addition, the rating options are reduced to 3, ranging from 1 (low anxiety) to 3 (high anxiety).

In addition, we will implement a visual analog scale (VAS), which provides an effective method of assessing children’s affective state as it offers a simple and easy to understand way of quantifying emotions. We will use the scale “Anxiety” by Gräßer et al [34]. This is based on a scale from 0 (not at all) to 10 (very strong). By simultaneously presenting an illustration the children can identify with and scaling the values from 0 to 10 on a line, children can express their emotional experience in a precise and differentiated way. For comparability between the children’s self-report and the impressions of the caregivers and the interviewers, we will also ask the caregivers and the interviewers to rate the patients’ pain perception on the same VAS.

**Table 1 table1:** Breakdown of the psychometric instruments administered (ie, questionnaires, visual analog scales, and self-designed questions) for each respondent group and measurement time.

Respondents and measurement time			Psychometric instrument
**Children**			
	Screening	STAIC-T^a^	
	Preintervention measurement	STAIC-S^b^ VAS^c^ anxiety PANAS-K^d^ SSQ-C^e^	
	Postintervention measurement	STAIC-S VAS anxiety PANAS-K VAS pain SSQ-C Adapted PXI^f^ for childreng Patient experience Presence	

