## Methods

### Hypotheses

In this study, we investigate whether targeted distraction from anxiety- and pain-inducing medical procedures through cooperative VR gaming can reduce experienced pain and anxiety while fostering well-being for both the patients and their caregivers. A list of our hypotheses is presented in Textbox 1. Hence, the primary outcome of the study is a reduction in pain and anxiety ratings of the patient (hypothesis 1) as well as an improvement in the caregiver’s emotional experience (hypothesis 2). Our intervention relies on targeted distraction through sensory immersion for the patient as well as cognitive immersion and game fun for the patient and caregiver. Thus, distraction from the medical procedure represents a further end point of the study (hypothesis 3 and hypothesis 5).

The smooth execution of the medical procedure, characterized by the cooperativeness of the patient and caregiver, the needlessness of sedation or fixation, and an uninterrupted flow, will be assessed as a secondary end point (hypothesis 4). Moreover, this study aims to evaluate the quality of SDVR with respect to the player experience of both patient and caregiver (hypothesis 5).

A list of hypotheses.

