**Caregivers**			
	Preintervention measurement	PANAS PANAS-C-P^g^ VAS anxiety (child)	
	Postintervention measurement	PANAS 0-P VAS anxiety (child) VAS pain (child) PXI^h^ Player experienceg	

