**Interviewers**			
	Observation	CHEOPS^i^ Self-designed questions for assessing procedure flow	

^a^STAIC-T: State-Trait Anxiety Inventory for children–trait anxiety.

^b^STAIC-S: State-Trait Anxiety Inventory for children–state anxiety.

^c^VAS: visual analog scale.

^d^PANAS-K: German translation of the Positive and Negative Affect Schedule for Children.

^e^SSQ-C: Child Simulator Sickness Questionnaire.

^f^PXI: Player Experience Inventory.

^g^PANAS-C-P: parent version of the Positive and Negative Affect Scale for Children.

^h^Sweet Dive VR only.

^i^CHEOPS: Children’s Hospital of Eastern Ontario Pain Scale.

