##### Simulator Sickness

Simulator sickness is a possible adverse side effect of VR exposure. To diagnose simulator sickness, we will use the Child Simulator Sickness Questionnaire adapted by Hoeft et al [42] and translated to German by us. The questionnaire comprises 7 items describing different symptoms summarized in dimensions “nausea,” “oculomotor,” and “disorientation.” Each symptom is rated on a 3-point scale ranging between 0 (“not at all”) and 3 (“very much”).

However, it should be noted that our target group will consist of children who are sick. Thus, it is likely that some participants, due to their illness, will experience symptoms that are also associated with simulator sickness. Therefore, we will ask the participants to rate their symptoms before (ie, before measurement) and after (ie, after measurement) the VR exposure.

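### Pain, part of the primary patient outcome, has no pre-procedure rating, so existing pain cannot be separated out or adjusted for; the cost is precision, not bias

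*Protocol article*

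**What the plan says.** The Hypotheses section of the protocol article states that "the primary outcome of the study is a reduction in pain and anxiety ratings of the patient", and ties this to hypothesis 1.

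Table 1 sets out the instruments by respondent and time:

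- Child, before: "STAIC-S^b^ VAS^c^ anxiety PANAS-K^d^ SSQ-C^e". No pain scale is listed.
- Child, after: the list opens with "STAIC-S VAS anxiety PANAS-K VAS pain SSQ-C". The four earlier instruments return and VAS pain is new.
- Caregiver, before: "PANAS PANAS-C-P^g^ VAS anxiety (child"), again without pain.
- Caregiver, after: the list includes "VAS anxiety (child) VAS pain (child").
- Interviewer: "CHEOPS^i^ Self-designed questions for assessing procedure flow", at the observation only.

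The Simulator Sickness section explains why the child rates those symptoms twice: "it is likely that some participants, due to their illness, will experience symptoms that are also associated with simulator sickness". The Randomization and Stratification section minimises on trait anxiety, age, type of intervention, previous experience with the procedure and sex. Current pain is not a factor.

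**The concern.** Anxiety, the other half of the patient primary outcome, has a pre-procedure value, and so do the sickness symptoms. Pain has none from any rater. The protocol's reason for rating sickness symptoms twice is that illness may already produce them, and that reason fits pain equally well. The section on confounding and influencing factors does not mention current pain.

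With one score after the procedure, pain the child brought to the room cannot be told apart from pain caused by the procedure. Variation in existing pain then stays in the residual error. A chance difference in existing pain between two arms of 39 would pass unseen into the pain comparison. A statistical analysis plan that is not shown cannot repair this, because no analysis can adjust for a value that was never collected.

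**Working it through.** **Inputs.** The Sample section gives 39 per group, a two-sided t test, alpha 0.05, power 80% and d of about 0.64. The Results section gives 39 children enrolled by November 2024, which is half of the planned 78. The pre/post pain correlation r is not given; I assume 0 to 0.5.

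**The plan's own figure.** The noncentral t calculation with 39 per group gives a detectable d of 0.643, and power of 79.7% at d = 0.64. The stated figure is reproduced.

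**Is there bias?** I simulated 40,000 trials with no treatment effect and existing pain added to procedural pain in both arms. The type I error of the post-only t test was 5.1% and the mean difference between arms was 0.00. The comparison is not systematically biased.

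**Gain from a baseline covariate.** If a fraction f of the children has a baseline and the rest carry a missing-indicator term, average residual variance is about 1 − f·r² times the unadjusted variance. The detectable d is 0.64 × √(1 − f·r²).

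| r (assumed) | Variance cut, f = 0.5 | Detectable d, f = 0.5 | Variance cut, f = 1 | Detectable d, f = 1 |
|---|---|---|---|---|
| 0 | 0% | 0.64 | 0% | 0.64 |
| 0.3 | 4.5% | 0.64 × 0.977 = 0.63 | 9% | 0.64 × 0.954 = 0.61 |
| 0.5 | 12.5% | 0.64 × 0.935 = 0.60 | 25% | 0.64 × 0.866 = 0.55 |

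The f = 1 columns show what a baseline from the start would have given. The f = 0.5 columns show what an amendment after 39 enrolments could give. If more children have been enrolled since November 2024, f is smaller and so is the gain.

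**Chance imbalance.** The standard error of the difference in mean existing pain is √(2/39) = 0.226 SD. A one-standard-error imbalance shifts the post-procedure pain difference by r × 0.226 SD: 0 at r = 0, 0.07 SD at r = 0.3 and 0.11 SD at r = 0.5. This takes no account of minimisation on procedure type, which would reduce it to some degree.

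**The case against.** The strongest reply is that the hypotheses need no baseline. Hypothesis 1 compares the pain level reported in the two groups, hypothesis 3 refers to pain during the procedure, and the sample size rests on a two-group t test. A post-only rating in a randomised trial answers all of these. That stands, and it is why this is a matter of precision.

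Four further points on that side:

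- The sickness comparison is imperfect. A pre-rating there serves to attribute symptoms to VR exposure within a child, whereas pain is compared between randomised arms. This also stands in part: the analogy supports collecting the value but does not make its absence an error.
- Procedure type is minimised and diagnosis is recorded. Both give partial protection, but neither captures differences in pain between children with the same procedure and diagnosis.
- The Pain section says the pain VAS is used in the same way as the anxiety VAS, which is rated twice. The natural reading is that this concerns the scale format, since Table 1 separates the two scales by time.
- Table 1 is not exhaustive, because it omits an interviewer VAS pain rating that the text describes. Even so, no section describes a pain rating before the procedure.

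A reader might go further and infer that existing pain is counted as procedural pain. The documents do not support this, because the recall wording of the pain VAS is not shown and may already ask about the procedure itself. Nor do they say that the children are post-operative or have a central line in place: the Sample section enrols children for catheter insertion, and a post-operative state is only an inference from Kirschner-wire removal. How many children have pain beforehand is not stated.

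**Conclusion.** The schedule is as described: neither child nor caregiver rates pain before the procedure, although pain is part of the primary patient outcome. Existing pain in these children can therefore be neither separated from procedural pain nor adjusted for. The between-group test of hypothesis 1 remains valid and is not systematically biased. The loss is precision, plus a chance imbalance that cannot be seen or directly corrected.

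The size runs from nil to modest. With r between 0 and 0.5 and a baseline in about half of the children, the detectable d lies between 0.64 and about 0.60. It is tempting to quote 0.55, but that needs r = 0.5 and a baseline in all 78 children, which is out of reach with 39 already enrolled. If most children start near zero pain, r may be close to 0 and the gain negligible. This is a cheap improvement worth making, not a flaw that threatens the trial.

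**What to change.** Add the existing VAS pain item, worded for current pain, to the pre-examination questionnaires of child and caregiver in Table 1, for all children still to be enrolled. Use each rater's value as the covariate for that rater's post-procedure VAS pain, with a missing-indicator term for children enrolled earlier. Allocation happens at registration, ahead of these questionnaires, and the article does not say when families learn their group. The item is best answered before they do, so that the covariate cannot be affected by allocation.

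The cost is one extra item per respondent in the electronic questionnaire and a short amendment. The 39 children enrolled by November 2024 will have no baseline.

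If the item is not added, state the pain outcome in the Hypotheses section as a lower post-procedure rating than control, in line with hypothesis 1, so that a within-child reduction is not implied.

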**Caregivers**			
	Preintervention measurement	PANAS PANAS-C-P^g^ VAS anxiety (child)	
	Postintervention measurement	PANAS 0-P VAS anxiety (child) VAS pain (child) PXI^h^ Player experienceg	
**Interviewers**			
	Observation	CHEOPS^i^ Self-designed questions for assessing procedure flow	

^a^STAIC-T: State-Trait Anxiety Inventory for children–trait anxiety.

^b^STAIC-S: State-Trait Anxiety Inventory for children–state anxiety.

^c^VAS: visual analog scale.

^d^PANAS-K: German translation of the Positive and Negative Affect Schedule for Children.

^e^SSQ-C: Child Simulator Sickness Questionnaire.

^f^PXI: Player Experience Inventory.

^g^PANAS-C-P: parent version of the Positive and Negative Affect Scale for Children.

^h^Sweet Dive VR only.

^i^CHEOPS: Children’s Hospital of Eastern Ontario Pain Scale.

##### Positive and Negative Emotions

To assess the participants’ affective state, we will use the positive affect negative affect schedule (PANAS) [35]. The questionnaire consists of 2 separate scales, one for positive affect (PA) and one for negative affect (NA). Each scale comprises a list of words that describe different emotions or moods. Respondents will be asked to indicate the extent to which they felt each of these words either “when thinking about the medical procedure” (before measurement) or “during the medical procedure” (after measurement).

For the caregivers, we will use the original questionnaire translated to German by Janke and Janke and Glöckner-Rist [36]. This version comprises 20 adjectives that describe emotional states. The rating scale describes the intensity with which these emotional states were experienced on a 5-point scale from 1 (not at all) to 5 (extremely). For the 2 dimensions PA and NA, the sum scores are formed from the intensity ratings of the corresponding items.

In addition to describing their own emotional experience, the caregivers assess the children’s emotional states using the parent version of the Positive and Negative Affect Scale for Children, which we will use in the German translation provided by Großheinrich [37]. The scale consists of 2 subscales to determine the children’s PA (12 items) and NA (15 items) according to the caregiver’s impression on a 5-point scale from 1 (very little or not at all) to 5 (extremely).

The participating children will be administered an adapted version of the original PANAS (PANAS-C) developed by Laurent et al [38]. To our knowledge, because no official German translation of the children’s version of the PANAS-C exists, we used this version as a starting point and compared the items with the German translations of the adjectives according to Janke and Glöckner-Rist [36]. As the PANAS-C comprises 30 items, rather than 20 items as in the version by Janke and Glöckner-Rist [36], additional adjectives for which no translation could be found were translated by the authors.

#### Pain

To measure the children’s perceived pain, we will use the VAS “Pain” by Gräßer et al [34], equal to the measurement of anxiety (as mentioned earlier). Again, we will ask the patients, the caregivers, and the interviewers for a rating.

The interviewers will rate the observed pain-associated behavior of the child using the Children’s Hospital of Eastern Ontario Pain Scale [39]. It can be used to monitor the effectiveness of interventions to reduce pain and discomfort in young children. The result is a pain score between 4 (no pain) and 13 (severe pain).

#### Player Experience

##### Overview

We will use the German translation of the Player Experience Inventory (PXI), which was developed by Graf et al [40], to assess the caregivers’ experiences while they play SDVR. The PXI consists of 10 dimensions that describe aspects of the player experience, allowing for a systematic analysis of the game design. Each dimension comprises 3 items, which are rated on a 7-point scale ranging from –3 (strongly disagree) to 3 (strongly agree).

For evaluating the caregivers’ experience, we will consider only the following constructs: “ease of control,” “goals and rules,” “challenge,” “meaning,” “curiosity,” and “mastery and immersion.” We will exclude the constructs “progress feedback,” “audiovisual appeal,” and “autonomy” from the evaluation of SDVR because the game does not have any audiovisual component for caregivers.

To date, there is no suitable and validated version of the PXI for children. As the PXI in its complete form is quite extensive and, in our experience, some item formulations are difficult for younger children to understand, we created a variant by selecting 1 item from each of the 10 dimensions that is clear and easy to understand. In the first round, 3 of the authors—an educator and health play specialist, a pediatric nurse with significant expertise in child-friendly medical language, and an entertainment computing specialist—independently selected 1 item per dimension that, in their opinion, met the criteria of representativeness for the dimension, child-appropriate concept complexity, and child-appropriate language. In the second step, the items for which there was no agreement between the 3 reviewers were discussed until consensus was reached. Moreover, we reduced the response options to a more child-friendly 5-point scale from −2 (strongly disagree) to +2 (strongly agree). It should be noted that this is a tentative, empirically unvalidated version. The data collected in the study may provide the basis for future efforts to develop a suitable player experience metric for children. For the sake of reproducibility and transparency, we included the final list of items in Multimedia Appendix 1.

The interviewers will be asked to assess the child’s player experience by rating the statements “The child had fun playing.”; “...was completely immersed in the play world.”; “...gave the caregiver clear, game-related instructions.”; “...understood what his role in the game was.”; “...had no problems with the controls of the game”; and “...was optimally challenged by the game” on a 7-point Likert scale.

##### Presence

According to our assumptions, playing a VR game creates presence, which can be explained as a redirection of the user’s attentional focus from the real to the virtual world. Hence, the experience of presence is an indicator of distraction from the medical situation. As there is no questionnaire designed for children to measure their sense of presence, we will use 5 items from the German Igroup Presence Questionnaire [41]. These 5 items describe how conscious the players were of the actual world and how real the virtual world seemed to them. The vocabulary used in these items is less abstract, which makes it easier for children to comprehend. The items are rated on a 7-point scale from 0 (strongly disagree) to 6 (strongly agree).

##### Simulator Sickness

Simulator sickness is a possible adverse side effect of VR exposure. To diagnose simulator sickness, we will use the Child Simulator Sickness Questionnaire adapted by Hoeft et al [42] and translated to German by us. The questionnaire comprises 7 items describing different symptoms summarized in dimensions “nausea,” “oculomotor,” and “disorientation.” Each symptom is rated on a 3-point scale ranging between 0 (“not at all”) and 3 (“very much”).

However, it should be noted that our target group will consist of children who are sick. Thus, it is likely that some participants, due to their illness, will experience symptoms that are also associated with simulator sickness. Therefore, we will ask the participants to rate their symptoms before (ie, before measurement) and after (ie, after measurement) the VR exposure.

